### 2002 **2.1 All-cause mortality**

2003 As described above in 1.1

2004 **2.2 Fatal and non-fatal cardiovascular events** including a) Coronary heart disease death, b)  
 2005 non-fatal myocardial infarction, c) fatal and non-fatal stroke and d) hospitalization for heart  
 2006 failure.

- 2007 **a) Coronary heart disease death** - Myocardial infarction, sudden cardiac death, rapid cardiac  
 2008 death (death after possible myocardial infarction), cardiac failure death (with coronary cause)  
 2009 and other coronary death.
- 2010 • *Myocardial infarction* - Autopsy or death certificate diagnosis, with definitive or suspected
  - 2011 diagnosis of myocardial infarction within 4 weeks of death.
  - 2012 • *Sudden cardiac death* - Death occurring within one hour of the onset of new cardiac
  - 2013 symptoms (ischemic chest symptoms or sudden collapse) or unwitnessed death after last

- being seen without new cardiac symptoms, and in each case, without any coronary disease (clinically or at autopsy) that could have been rapidly fatal.
- *Rapid cardiac death (death after possible myocardial infarction)* - Death within 1-24 hours of the onset of severe cardiac symptoms unrelated to other known causes. Death in hospital with possible myocardial infarction (i.e. participants who have had typical ischemic pain and whose ECG and enzyme results fulfill the criteria for definitive MI and in whom there is no good evidence for another diagnosis for the event).
  - *Cardiac failure (with coronary cause)* - Death due to heart failure (prior NYHA Class III-IV dyspnea), without any defined non-coronary cause.
  - *Other coronary death* - Any death where the underlying cause is certified as coronary (and where there is no evidence of non-coronary cause of death, clinically or at autopsy).

**b) Non-fatal myocardial infarction** - (American College of Cardiology & European Society of Cardiology definition) 

*Criteria for acute, evolving or recent MI.* Either one of the following criteria satisfies the diagnosis for an acute, evolving or recent MI:

- (1) Typical rise in troponin or CK-MB as biochemical markers of myocardial necrosis with at least one of the following:
  - ischemic symptoms;
  - development of pathologic Q waves on the ECG;
  - ECG changes indicative of ischemia (ST segment elevation or depression) OR coronary artery intervention (e.g. coronary angioplasty).
- (2) Pathologic findings of an acute MI.

*Criteria for established MI.* Any one of the following criteria satisfies the diagnosis for established MI:

- Development of new pathologic Q waves on serial ECGs. The patient may or may not remember previous symptoms. Biochemical markers of myocardial necrosis may have normalized, depending on the length of time that has passed since the infarct developed.
- Pathologic findings of a healed or healing MI.

**c) Fatal and non-fatal stroke** - Fatal stroke will be defined as any death due to the rapid onset of a new neurological deficit attributed to obstruction or rupture in the intra-cranial or extra-cranial cerebral arterial system. Stroke will be defined according to the World Health Organization (WHO) definition as 'rapidly developing clinical signs of focal (or global) disturbance of cerebral function lasting more than 24 hours (unless interrupted by surgery or death) with no apparent cause other than of vascular origin' . This definition excludes cases of primary cerebral tumor, cerebral metastasis, subdural hematoma, post seizure palsy, brain trauma, and transient ischemic attack.

In Australia and the U.S., virtually all symptomatic strokes occurring in non-institutionalized patients are investigated by imaging with CT and/or MRI scanning. A National Stroke Audit carried out on a sample of patients throughout Australia in 2007 (<http://www.strokefoundation.com.au/images/stories/healthprofessionals/national%20stroke%20audit%20clinical%20report%20acute%20services.pdf>), including remote areas, found that 91% of all patients received a CT scan or MRI within the first 24 hours after stroke. Given that people in remote areas in Australia are likely to be those not receiving CT scans or MRI, we expect all Australian ASPREE stroke cases will have accompanying CT or MRI scans as part of their usual care. In the U.S., 78 - 98% of patients who present to the hospital with acute symptoms of stroke have brain imaging at or shortly after the time of presentation . CT scans, MRI reports and

ECG reports of rhythm disturbances (e.g., atrial fibrillation) will be included for consideration in the endpoint determination.

Because hemorrhagic stroke is both an endpoint and an adverse event, sub-classification will be used for strokes. Ischemic stroke is defined as a stroke for which a CT scan performed within 28 days of the onset of symptoms showed an area of low attenuation or an abnormal appearance in the vascular territory that corresponded to the recent symptoms and signs; or MRI showed a clinically relevant area of increased signal on diffusion weighted imaging, a slight hypointensity with or without mass effect on T1-weighted images, a bright area of hyper intensity with or without mass effect on T2-weighted images, or evidence of recent infarction on diffusion weighted MRI imaging. Alternatively cerebral infarction may be confirmed by autopsy. The TOAST classification for subtype of acute ischemic stroke will be utilized , in which both clinical features and ancillary tests (laboratory, radiology, and ultrasonography) are used to categorize five subtypes:

1. large artery atherosclerosis (embolus/thrombosis)
2. cardio embolism (high risk/medium risk)
3. small-vessel occlusion (lacunae)
4. stroke of other determined etiology
5. stroke of undetermined etiology
  - a. two or more causes identified
  - b. negative evaluation
  - c. incomplete evaluation

| Features                                                         | Subtype                      |                 |                                  |              |
|------------------------------------------------------------------|------------------------------|-----------------|----------------------------------|--------------|
|                                                                  | Large-artery atherosclerosis | Cardio embolism | Small-artery occlusion (lacunae) | Other causes |
| Clinical                                                  |                              |                 |                                  |              |
| Cortical or cerebellar dysfunction                               | +                            | +               | -                                | +/-          |
| Lacunar syndrome                                                 | -                            | -               | +                                | +/-          |
| Imaging                                                   |                              |                 |                                  |              |
| Cortical, cerebellar, brain stem, or subcortical infarct >1.5 cm | +                            | +               | -                                | +/-          |
| Brain stem, or subcortical infarct <1.5cm                        | -                            | -               | +/-                              | +/-          |
| Tests                                                     |                              |                 |                                  |              |
| Stenosis of extracranial internal carotid artery                 | +                            | -               | -                                | -            |
| Cardiac source of emboli                                         | -                            | +               | -                                | -            |
| Other abnormality on tests                                       | -                            | -               | -                                | +            |

**Table 1.** A summary of the classification for ischemic stroke. Features of Trial of Org 10172 in Acute Stroke Treatment (TOAST) classification of subtypes of ischemic stroke .

Hemorrhagic stroke - is defined as a stroke in which a CT scan demonstrates an area of hyperdensity within the brain parenchyma with or without extension into the ventricles or subarachnoid space or, for scans performed beyond 1 week, an area of attenuation with ring enhancement after injection of contrast; MRI showing an area of hypointensity or isointensity on T1-weighted images or an area of marked hypointensity on gradient echo and T2-weighted images, or by autopsy demonstrating the origin of the hemorrhage as the cerebral parenchyma. Rarer causes and sites of intracerebral hemorrhage such as underlying arteriovenous malformation and spinal cord hemorrhage will be documented. Distinction between ischemic and hemorrhagic stroke can only be made with appropriate imaging. As noted above, CT or

MRI scanning is now undertaken as part of the investigation of virtually all cases of stroke in both the U.S. and Australia. Results of such imaging will be sought routinely by the ASPREE investigators for presentation to the endpoint committee. To complement our use of the TOAST classification for thrombo-embolic stroke, we will quantify the extent of intracerebral hemorrhage by assessing hemorrhage site and volume by CT or MRI. Volume will be assessed by utilizing the ABC/2 formula with hemorrhage sites as lobar, basal ganglionic or brain stem.

**d) Hospitalization due to cardiac failure** - Hospital discharge diagnosis of cardiac failure will trigger an assessment by the endpoint committee. Hospitalization for heart failure is defined as an unplanned overnight stay, or longer, in a hospital environment (emergency room, observation unit or inpatient care) or similar facility. Heart failure is defined as a patient having typical symptoms (e.g., dyspnea, fatigue) that can occur at rest or on effort that is characterized by objective evidence of an underlying structural abnormality or cardiac dysfunction that impairs the ability of the ventricle to fill with or eject blood (particularly during exercise). The diagnosis of heart failure may be further strengthened by a beneficial clinical response to treatment(s) directed towards amelioration of symptoms associated with this condition.

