## 1991 **2. Secondary Endpoints:**

- 1992 1. All-cause mortality
- 1993 2. Fatal and non-fatal cardiovascular events including a) coronary heart disease
- 1994 death, b) non-fatal myocardial infarction, c) fatal and non-fatal stroke and d)
- 1995 hospitalization for heart failure.
- 1996 3. Fatal and non-fatal cancer, excluding non-melanoma skin cancer
- 1997 4. Dementia
- 1998 5. Mild cognitive impairment (MCI)
- 1999 6. Physical ADL disability
- 2000 7. Depression
- 2001 8. Major hemorrhagic events

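### The sudden cardiac death criterion excludes rapidly fatal coronary disease where its heading and neighbouring criteria call for excluding non-coronary disease, so the coronary-death component is wrong as written

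*Protocol*

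**What the plan says.** The second secondary endpoint in Appendix 1, section 2 is "Fatal and non-fatal cardiovascular events including a) coronary heart disease" death as component (a), with non-fatal infarction, stroke and heart failure hospitalization as the other three components. Section 2.2(a) divides coronary heart disease death into five categories, beginning "Myocardial infarction, sudden cardiac death, rapid cardiac" death.

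Sudden cardiac death has two routes: death within one hour of new cardiac symptoms (ischemic chest symptoms or sudden collapse), or an unwitnessed death in someone last seen without such symptoms. Both carry the same condition: "in each case, without any coronary disease (clinically or at autopsy) that could have been rapidly fatal".

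Three neighbouring categories set their exclusions the other way:

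- Rapid cardiac death: death within 1-24 hours "of the onset of severe cardiac symptoms unrelated to other known causes".
- Cardiac failure with coronary cause: "without any defined non-coronary cause".
- Other coronary death: underlying cause certified as coronary, and "where there is no evidence of non-coronary cause of death, clinically or at autopsy".

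The rapid cardiac death bullet also covers in-hospital death with possible myocardial infarction, which it explains as participants with typical pain "whose ECG and enzyme results fulfill the criteria for definitive MI and in whom there is no good evidence for another diagnosis".

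Protocol section 5.2 says that every secondary endpoint has objective ascertainment criteria, set out in Appendix 1, and is reviewed by the Endpoint Adjudication Committee. Section 12.3.1 says the committee is blinded to treatment. Section 5.5 requires at least two reviewers, with a third if they disagree.

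**The concern.** A category of coronary death should exclude competing non-coronary explanations. This one excludes the disease being counted. It can therefore fail in two ways: true coronary deaths are refused, and non-coronary sudden deaths are admitted. A ruptured aorta or pulmonary embolism that presents as sudden collapse or as an unwitnessed death meets the criterion if no rapidly fatal coronary disease is found.

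Because section 5.2 makes Appendix 1 the adjudication standard, this is the operative rule for part of the main cardiovascular endpoint. That endpoint is central to weighing aspirin's benefit against its bleeding harm. If adjudicators silently apply what they take to be the intent, the rule in use is no longer the written one, and two reviewers may resolve the contradiction differently.

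**Working it through.** **1. The text.** No stated figure turns on this clause, so the check is mainly a comparison of the criteria.

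- Sudden cardiac death requires the absence of rapidly fatal *coronary* disease.
- Cardiac failure death requires the absence of a defined *non-coronary* cause.
- Other coronary death requires the absence of evidence of a *non-coronary* cause, with the same reference to clinical or autopsy findings as the disputed clause.
- Rapid cardiac death requires symptoms not explained by *other* causes.

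The first runs against the other three and against its parent heading. The clause is continuous, with no gap or table break inside it, and no other place in the protocol defines sudden cardiac death. A dropped 'non-' is the natural explanation.

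**2. Literal application.**

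- *Sudden collapse, severe coronary disease at autopsy.* Fails sudden cardiac death. It may still count as a myocardial infarction death (autopsy or death certificate diagnosis, definitive or suspected infarction within 4 weeks of death) or as other coronary death if so certified. The loss is partial.
- *Unwitnessed death from a non-coronary cause, no rapidly fatal coronary disease.* Passes. Nothing else in the bullet removes it, and no other category can take it out again.

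**3. The plan's own power figure, for context.** Inputs from Appendix 2: age shares 50%, 30% and 20% (the last combining 15% and 5%); rates 17, 25 and 38 per 1000; 1.2 per 1000 subtracted for hemorrhagic stroke; 19,000 participants; 4.7 years at risk; hazard ratio 0.858; two-sided alpha 0.05.

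- Placebo rate: 0.5 × 17 + 0.3 × 25 + 0.2 × 38 = 23.6; less 1.2 = 22.4 per 1000, as stated.
- Expected events: 19,000 × 4.7 × 0.0224 × (1 + 0.858)/2 = 1,858.
- Power (Schoenfeld): Φ(√1858/2 × |ln 0.858| − 1.96) = 0.91, against 90% stated. Events needed for 90%: 1,792.

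The stated power reproduces, and correcting the clause changes none of these numbers.

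**4. Sensitivity, under an assumption.** The documents give no share of sudden deaths. Suppose a fraction f of placebo endpoint events is replaced by deaths on which aspirin has no effect. The hazard ratio becomes (1 − f) × 0.858 + f:

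- f = 2%: hazard ratio 0.861, power 0.90
- f = 5%: hazard ratio 0.865, power 0.88
- f = 10%: hazard ratio 0.872, power 0.84

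These values of f are illustrative and not estimates.

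**5. The rapid cardiac death bullet.** A label of possible infarction is explained by results that meet the criteria for definitive infarction. Label and text disagree, and as worded the bullet largely duplicates the myocardial infarction category. No neighbouring text shows which was meant.

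**The case against.** The strongest reply is that reach and consequence are small. The clause governs one of five categories within one of four components of one of eight secondary endpoints. The primary endpoint uses death from any cause. Many sudden coronary deaths re-enter through the infarction or other coronary categories. Fatal bleeds stay in the major hemorrhage endpoint (Appendix 1, section 2.8), so that harm is not lost, and most fatal intracranial bleeds already count as fatal stroke in the same composite, since the stroke definition includes arterial rupture. Blinded dual review makes differential error between arms unlikely, and experienced adjudicators may well apply the evident intent. All of this stands as a limit on the consequence. None of it makes the printed criterion right.

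One might also read the clause as a sorting rule that sends deaths with proven coronary disease to the infarction category. The text states no such order, and what remained would be sudden deaths without rapidly fatal coronary disease, still counted as coronary.

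A reader might infer more: that coronary deaths are lost wholesale, that bleeding deaths are systematically counted as coronary, or that the comparison is biased for or against aspirin. The documents do not support this. Recapture is available for the first, the second holds only for deaths that are sudden or unwitnessed and fall outside the stroke definition, and no actual misclassification is shown.

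A reader might also try to size the problem from the cardiovascular death shares in Table 1. Those rates include cerebrovascular deaths, describe a general population where the trial excludes people with prior cardiovascular events, and still need an assumed sudden share. The result would count deaths judged under the rule, not deaths misclassified.

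**Conclusion.** The criterion is wrong as written and should be fixed. It contradicts its heading and its neighbours, nothing elsewhere repairs it, and section 5.2 makes it the adjudication rule. Applied literally, some true coronary deaths fail the category, and sudden or unwitnessed non-coronary deaths can be counted as coronary.

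The damage is confined to the coronary-death component of the cardiovascular secondary endpoint, and its size cannot be determined from the documents. With blinded adjudication, the main expected effect is dilution of that endpoint. Non-coronary deaths that aspirin itself affects, such as bleeds, are a possible exception and could shift the estimate. This rests on the criterion being applied as printed, which is not known.

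The possible-infarction wording is a separate and weaker inconsistency. A reader might infer that a 'not' was dropped, but that cannot be established from the text. The effect on the endpoint is probably small, because a death meeting definitive infarction criteria is coronary under either label and a certified suspected infarction is already covered.

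**What to change.** In Appendix 1, section 2.2(a), insert 'non-' before 'coronary disease' in the sudden cardiac death bullet, so that the clause rules out non-coronary disease, found clinically or at autopsy, that could have been rapidly fatal. Make the same change in any adjudication charter or form that repeats the text.

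Have the Endpoint Adjudication Committee confirm, blinded to treatment, which rule it applied to any sudden deaths already adjudicated, and re-review those judged under the printed wording. Appendix 2 reports recruitment numbers already achieved, so there may be such deaths.

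Separately, have the committee state what possible myocardial infarction was meant to cover in the rapid cardiac death bullet, and bring label and definition into line.

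The cost is a few words of amendment and a small blinded review. Sample size, power and the primary analysis are unchanged.

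### The sudden cardiac death definition excludes coronary disease where its neighbouring subtypes exclude non-coronary causes, so as written it contradicts the coronary heart disease death category it belongs to

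*Protocol*

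**What the plan says.** Protocol Appendix 1, section 2.2, builds the cardiovascular secondary endpoint from CHD death, non-fatal myocardial infarction, stroke and hospitalization for heart failure. Part (a) splits CHD death into five subtypes; the list opens "Myocardial infarction, sudden cardiac death, rapid cardiac" death, then adds cardiac failure death with a coronary cause and other coronary death.

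Sudden cardiac death has two limbs: death within one hour of new cardiac symptoms, and unwitnessed death in someone last seen without them. The wording "symptoms (ischemic chest symptoms or sudden collapse) or unwitnessed death after last" shows that a sudden collapse is enough to count as a cardiac symptom. A final clause then applies to both limbs: "in each case, without any coronary disease (clinically or at autopsy) that could have been rapidly fatal".

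Section 5 of the protocol refers to Appendix 1 for the detailed endpoint definitions. Section 5.2 says that the ascertainment criteria for the secondary endpoints are set out there and that the Endpoint Adjudication Committee reviews each endpoint. The clause is therefore the rule the committee works to.

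**The concern.** A category of coronary death cannot sensibly require that no lethal coronary disease be found. Taken at its word, the clause disqualifies the finding that would best support the label and contains no exclusion of a competing non-coronary cause. Because collapse alone qualifies and unwitnessed deaths are admitted, that missing exclusion is the main safeguard against labelling other sudden deaths as coronary.

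The error is not neutral for an aspirin trial. Vascular prevention is the benefit sought and bleeding the principal harm, so a rule that could count a fatal extracranial bleed as a CHD death blurs the two. Section 6.2 also excludes people with diagnosed infarction, angina or coronary revascularization, so coronary disease may first come to light at autopsy, which is the finding the clause rejects.

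**Working it through.** **1. The subtypes side by side (Appendix 1, section 2.2(a)).**

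| Subtype | What it excludes or requires | Direction |
|---|---|---|
| Myocardial infarction | "Autopsy or death certificate diagnosis, with definitive or suspected" infarction within 4 weeks of death | Positive coronary evidence |
| Sudden cardiac death | "in each case, without any coronary disease (clinically or at autopsy) that could have been rapidly fatal" | Excludes **coronary** disease |
| Rapid cardiac death | "the onset of severe cardiac symptoms unrelated to other known causes" | Excludes other causes |
| Cardiac failure | "without any defined non-coronary cause" | Excludes **non-coronary** cause |
| Other coronary death | "where there is no evidence of non-coronary cause of death, clinically or at autopsy" | Excludes **non-coronary** cause |

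Three of the other four subtypes rule out competing causes, and the fourth asks for positive coronary evidence. Only sudden cardiac death rules out coronary disease. The word 'non-coronary' appears intact in two neighbouring entries, so a fault in reading the PDF is unlikely. Nothing elsewhere in the protocol corrects the clause.

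**2. Who is removed under the literal rule.** A witnessed collapse with severe coronary disease at autopsy fails the sudden cardiac death definition. It can still be a CHD death by two routes: an infarction diagnosis within 4 weeks of death, or "Any death where the underlying cause is certified as coronary". Only deaths that satisfy no other subtype are lost from CHD death and from the composite.

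**3. Who is added.** A sudden collapse with death within the hour, or an unwitnessed death, with no potentially fatal coronary disease, meets the definition whatever the true cause. Examples are an extracranial bleed, pulmonary embolism or aneurysm rupture. A fatal intracranial arterial rupture is already in the composite as stroke under section 2.2(c), so it adds no event there, although it could be misplaced within the components.

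**4. What the plan's own figures can show (Appendix 2, secondary outcome 2).**
- Placebo rate: 0.5 × 17 + 0.3 × 25 + 0.2 × 38 = 23.6; less 1.2 for hemorrhagic stroke = 22.4 per 1,000 per year, as stated.
- Expected events: 19,000 × 4.7 × 0.0224 × (1 + 0.858)/2 = 1,858.
- Events needed for 90% power at two-sided 0.05 (Schoenfeld): 4 × (1.960 + 1.282)² / (ln 0.858)² = 1,792.
- Power with 1,858 events: 91%, against the stated 90%. The plan's figure reproduces.

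None of these inputs depends on the disputed clause. The protocol gives neither the share of cardiovascular events that are sudden deaths nor the share of those that would be misclassified, so no change in hazard ratio or power can be derived from it.

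**5. A check on the most extreme reading, that the hazard ratio could reach 1.** This is hypothetical. Suppose a share s of placebo cardiovascular events were misclassified deaths with hazard ratio 1.23, the figure Appendix 2 gives as *detectable* for major bleeding, not as expected. Then (1 − s) × 0.858 + s × 1.23 = 1 gives s = 0.142/0.372 = 38%. Placebo events number 9,500 × 4.7 × 0.0224 = 1,000, so about 382 would have to be such deaths. At Appendix 2's 11 per 1,000, all placebo major bleeds over the same time, fatal or not, number 9,500 × 4.7 × 0.011 = 491. With misclassified deaths at hazard ratio 1, the composite never reaches 1.

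**The case against.** The strongest reply is that this is a slip in drafting that experienced adjudicators would read through. Under section 5.5 at least two members review each case, and section 12.3.1 has them blinded to treatment. They work under a heading that says coronary death, beside definitions that point the right way. No document shows that the clause was applied literally. This stands as a reason not to assume harm. It does not remove the contradiction: the committee must either apply a wrong rule or depart from the written one without a record of doing so.

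Three stronger readings are tempting, and the reply is right about each.
- *True coronary deaths vanish from the endpoint.* Many would return through the infarction and other coronary death routes. Losing the rest lowers the event count but does not by itself move the hazard ratio, unless those deaths respond differently to aspirin.
- *Fatal bleeding is hidden.* Section 2.8 counts a fatal hemorrhage as a major hemorrhagic event, and nothing in the protocol takes it out of that endpoint. The one-hour limit on the witnessed limb would also keep out most fatal gastrointestinal bleeds.
- *Power falls materially, or the hazard ratio passes 1.* Any such figure needs an assumed share of sudden deaths, all taken as misclassified, with an assumed effect. The protocol supplies none of these.

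**Conclusion.** The definition is wrong as written: an internal contradiction between the clause, its parent heading and its neighbours. That the intended word was 'non-coronary' is an inference, though a strong one from the parallel wording. The reach is limited to one subtype of one component of one secondary endpoint. The primary endpoint uses death from any cause (section 5.1) and is untouched, as is the major hemorrhage endpoint. If the clause was applied literally, the CHD death component would be the most distorted. The direction for the composite would be some dilution through added non-coronary deaths, of a size the protocol does not allow anyone to state. This is a should-fix correction.

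**What to change.** In Appendix 1, section 2.2(a), change the clause so that it excludes any *non-coronary* disease, clinically or at autopsy, that could have been rapidly fatal. Issue the corrected text to the Endpoint Adjudication Committee and record which wording it has been using. If it was the printed wording, re-check the sudden and unwitnessed deaths, blind to treatment. Include those rejected as sudden cardiac death as well as those accepted. Complete this before unblinding, since redefining a component afterwards would look data-driven.

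The cost is a one-word amendment, a query to the committee and, only if needed, a second look at case files already collected. A time limit on when an unwitnessed decedent was last seen alive is a separate question that this contradiction does not raise, and none is proposed here.
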